## Introduction

### Background and rationale {6a}

Severe trauma is the leading cause of mortality in young adults in developed countries and is the third cause of overall death in the USA [1]. Death occurs within the first 48 h among 87% of trauma patients with fatal outcome, and the first cause of death at 24 h is massive bleeding [2, 3]. Hemorrhagic shock is preventable with adequate strategies including early control of the active source of bleeding and an optimization of initial resuscitation called “damage control resuscitation” [4]. The concept of damage control resuscitation consists of a combination of early administration of blood products, control of post-traumatic coagulopathy, and a reduction of crystalloid infusion and maintaining permissive hypotension. This strategy aims at treating hypovolemia and coagulation disorders while avoiding dilution coagulopathy [4]. International guidelines for blood product administration recommend the transfusion of packed red blood cell (RBC) and fresh frozen plasma (FFP) as soon as possible with RBC/FFP ratio between 1:1 and 2:1 [5, 6].

Early administration of coagulation factors with FFP has been highlighted in the prehospital setting suggesting a potential beneficial effect on mortality [7]. However, FFP administration may be delayed due to logistical reasons such as transport and immediate availability. The administration of four-factor prothrombin complex concentrate (PCC) has emerged as an alternative to early administrate coagulation factors and is used to treat post-traumatic coagulopathy in diverse European countries [8, 9]. A strategy combining fibrinogen and four factor-PCC has decreased blood product consumption [8]. The reduction of blood product consumption is meaningful since blood transfusion is associated with post-traumatic infectious complications [10] and is a risk factor for multiple organ failure after severe trauma [11]. Recently, an open-label randomized controlled trial comparing a classic massive transfusion protocol to a tailored administration of procoagulant concentrates, including PCC and fibrinogen, also showed a decrease in RBC transfusion resulting in less patients requiring massive transfusion [12]. However, there is no randomized controlled double-blind study assessing the impact of PCC in addition to a classic massive transfusion protocol including fibrinogen administration and blood product transfusion with RBC and FFP [13].

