#### Outcomes {12}

The primary outcome is the total number of blood products transfused within the first 24 h after hospital admission, including RBC, FFP, and platelets. The choice of this primary outcome is based on the following rationale. First, a recent randomized control trial exploring the effect of vasopressin use after severe trauma on the same endpoint [20], Second, even if transfusion is considered a pillar in the management of acute bleeding, blood products are associated with adverse events and poor clinical outcome [11, 21]. Third, mortality after severe trauma is a complex process depending on hemorrhage but also on traumatic brain injury and pre-existing medical conditions, specifically in elderly patients [22]. We thus believe that 24h total blood consumption is an accurate proxy of the severity of the bleeding until the hemorrhage stops.

Secondary outcome measures are (1) number of separate units (and volume) of RBC, FFP, and platelets and transfused in the first 24 h; (2) time to achieve prothrombin time ratio < 1.5; (3) time to hemostasis, defined as the time necessary to control bleeding in the surgical field (operative field is dry without further foreseeable homeostatic procedures) or to control contrast blush after embolization during an interventional radiology (no more dye flushing); (4) number of thrombo-embolic events at 28 days; (5) mortality at 24 h and 28 days; (6) intensive care unit (ICU)-free days (number of in-hospital days outside ICU) within the first 28 days; (7) ventilator-free days during ICU stay within the first 28 days; (8) hospital-free days within the first 28 days; (9) hospitalization status at day 28; (10) GOSE for patients with brain lesions on initial scan; and (11) cost of each strategy at days 8 and 28. Cost analyses will be performed on expensive care: blood products and procoagulant treatments administered, imaging exams, surgeries, and length of stay in each healthcare unit.

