#### Participant timeline {13}

All consecutive trauma patients admitted directly from the injury scene who require RBC transfusion with a risk of massive transfusion are screened on admission. Eligible patients are then rapidly enrolled by the study investigator. They should be randomized and treated accordingly within 60 min post-admission. After patient treatment, follow-up includes hourly visits until 6 h post-admission, as well as visits at 12 and 24 h to measure prothrombin ratio, assess hemorrhage control and monitor adverse events. Thrombo-embolic events are under special scrutiny during the entire hospital stay because they are frequently expected adverse effects of PCC treatment. Each suspicious thrombo-embolic event should be confirmed with venous Doppler echography or angiography and treated following standard practice. Thromboprophylaxis is left to physician discretion. Patients are followed for 28 days with the last visit aiming at collecting the Glasgow outcome scale extended (GOSE) for patients with brain lesions on initial cerebral imaging, mortality, and place of living (Fig. 1).

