##### Analysis of the main outcome

The main outcome is the total blood consumption (RBC, FFP, and platelets). It will be analyzed after verification that the time spent in the study up to H24 is not significantly different between the two groups. If this duration is not different, the total number of units transfused over 24 h between the two groups will be compared using a bilateral student intent to treat *t* test (if the application conditions are not met, we will use a non-parametric Mann-Whitney *U* test). If the duration is different, the amount of blood products used per hour between the two groups will be compared using an intention-to-treat Student *t* test (= total number of bags transfused over 24 h divided by the time spent in research during the first 24 h), in order to control for an attrition bias created by patients who died before 24 h.

The per-protocol analysis will be performed on patients who actually received treatment within 1 h of admission to the hospital.

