##### Secondary outcome analysis

We will use the same strategy as for the primary endpoint in order to compare each quantity of RBC, FFP, and platelets, independently; i.e., a Student’s *t* test (if the application conditions are not met, we will use a non-parametric test).

Comparison by a Student’s *t* test (if the application conditions are not met, we will use a nonparametric test) of the values of the Quick Time between the two groups.

The delay between the time of the trauma and clinical hemorrhage control will be compared between the two randomization groups by a Student’s *t* test (if the application conditions are not met, we will use a nonparametric test).

The number of thromboembolic events at D28 will be recoded as a qualitative variable. At least one event (pulmonary embolism or deep vein thrombosis) will be required for this variable. It will then be compared using the chi^2^ test between the two groups (when the conditions for the application of the chi^2^ test are not met, the Fisher’s test will be used).

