##### Calculation of the cost of each of the strategies

An average cost of care will be calculated for each group. Micro-costing and gross-costing methods will be used to reconstitute the cost of the hospital stay. Thus, data on the consumption of care will be collected prospectively throughout the entire length of the stay in intensive care (the number and nature of blood products and drug treatments used, additional examinations performed, and the length of stay in each care unit). In this way, we can calculate an average cost of the resuscitation stay in each group. The cost of the overall stay will be reconstituted using the modified GHM method, and it will be based on hospital cost accounting data (calculated within the framework of the ENC: national scale of costs).

Comparison of the cost of the two strategies: The difference in costs between the groups will be tested by a Student’s test or by a non-parametric test (Mann-Whitney tests) in case of non-Gaussian distribution. The choice of the test will be made with regard to the distribution of costs in each group (Shapiro-Wilk test, on raw data or, if necessary, on transformed data). If the distribution of costs is not Gaussian, the construction of the confidence interval of the average cost will be based on the non-parametric bootstrap method.

Deterministic and probabilistic sensitivity analyses will be performed to test the robustness of our estimates. Multivariate analyses will also be implemented to take into account censoring (death and follow-up time) in our cost analyses.

Mortalities at 24 h and 28 days will be compared between the two groups using the Kaplan-Meier model. Length of stay will be compared with a Student’s *t* test (if the application conditions are not met, we will use a non-parametric test).

The GOSE at 28 days will be compared with a Student’s *t* test (if the application conditions are not met, we will use a non-parametric test). The locations of the patient’s hospitalization at 28 days will be compared between the two groups using the chi^2^ test (when the application conditions of the chi^2^ test are not met, Fisher’s test will be used).

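### Time to haemorrhage control is defined from admission but analysed from the trauma, with a t test or unnamed nonparametric test and no rule for patients who die before control

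*Protocol article*

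**What the plan says.** Three places in the protocol article describe this endpoint.

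- **Objectives {7}**: the interval runs from admission to control of haemorrhage during a surgical and/or radiological procedure (dry operative field, or no further contrast blush).
- **Outcomes {12}**: "time to hemostasis, defined as the time necessary to control bleeding in the surgical field", or to control blush after embolisation. The event is the same, but no starting point is given.
- **Secondary outcome analysis, under {20a}**: "The delay between the time of the trauma and clinical hemorrhage control will be compared between the two randomization groups", and this is done "by a Student’s *t* test (if the application conditions are not met, we will use a nonparametric test").

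No section says how a patient enters this comparison who dies before control or who never has a procedure.

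The article does deal with early death elsewhere. For the primary outcome it switches to units per hour if time in study differs between arms, "in order to control for an attrition bias created by patients who died before 24 h". For costs: "Multivariate analyses will also be implemented to take into account censoring (death and follow-up time) in our cost analyses". For mortality: "Mortalities at 24 h and 28 days will be compared between the two groups using the Kaplan-Meier model".

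**The concern.** There are two separate problems.

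**Origin.** Time from trauma and time from admission are different variables. They differ by the pre-hospital interval, which is over before study treatment can act: after admission and enrolment, "They should be randomized and treated accordingly within 60 min post-admission". A statistician who follows the analysis section reports a number that does not answer the stated objective. One who follows the objective departs from the analysis section.

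**Method.** A t test or a rank test needs a value or a rank for every patient. A patient who dies still bleeding has no time to control. The background section says of this population that "the first cause of death at 24 h is massive bleeding", so such patients are to be expected. If they are left out, the comparison is restricted to patients selected after randomisation by surviving to control. Long control times are the ones most often cut off by death, so the arm with more early deaths loses more of its long times and looks faster.

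**Working it through.** The article gives no SD, mean or event rate for this endpoint, so there is no planned figure to reproduce. The wording comparison is set out above. The sizes below rest on assumed inputs, labelled as such.

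**1. Noise from the trauma origin**

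Assume that pre-hospital time is independent of arm and of in-hospital time. Then

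variance ratio = (SD_hosp² + SD_pre²) / SD_hosp².

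With an assumed SD_pre of 1 h:

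| Assumed SD_hosp | Variance ratio | Increase |
|---|---|---|
| 3.9 h | (15.2 + 1)/15.2 | about 6.5% |
| 3 h | (9 + 1)/9 | 11% |
| 2 h | (4 + 1)/4 | 25% |

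The 3.9 h is the SD of the lognormal used in step 2. In the 2 h case, a comparison that had 80% power from admission has power Φ(2.80/√1.25 − 1.96) = Φ(0.55), about 71%, from trauma. Because the added interval precedes randomisation, its expected contribution to the difference between arms is zero.

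**2. Shift if only observed times are compared**

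Assume that true control times are identical in both arms: lognormal, median 3 h, log-SD 0.8. Then

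- mean = 3 × exp(0.8²/2) = 4.13 h;
- SD = 4.13 × √(exp(0.8²) − 1) = 3.9 h.

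Let death before control occur at a constant hazard h, independent of control time. With f the density of control time,

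- proportion with a value = ∫ f(t) exp(−ht) dt;
- observed mean = ∫ t f(t) exp(−ht) dt divided by that proportion.

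| Death hazard per hour | With an observed time | Mean observed time |
|---|---|---|
| 0.03 | 88.9% | 3.75 h |
| 0.04 | 85.7% | 3.65 h |
| 0.08 | 74.6% | 3.31 h |

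With no true difference between arms, the spurious difference is:

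- 0.03 vs 0.08: 3.75 − 3.31 = 0.44 h, in favour of the arm with more deaths;
- 0.03 vs 0.04: 3.75 − 3.65 = 0.10 h;
- equal hazards: nil.

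The first contrast is deliberately large: about 11% against 25% die before control.

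**3. A second set of assumptions**

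Here the control times have a mean of about 184 min in both arms, and 11% to 19% of the control arm die before control, depending on how strongly a shared severity factor links slow control with death. If the treated arm has half the control arm's death hazard, its observed mean is spuriously 5 to 10 min longer. At a quarter of the hazard it is 8 to 18 min longer. At equal hazards the difference is about zero. The direction agrees with step 2.

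**The case against.** **Exclusion is not stated.** A reader might infer that the plan drops patients who die before control. It does not say so. This is a condensed article, and a separate statistical analysis plan could assign such patients a worst rank under the nonparametric option. This stands, so the selection problem is conditional. It does not remove the point: the fallback is triggered by failed test conditions, not by missing times. A t test is also the named first choice for a time that some patients never reach.

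**The origin does not bias the comparison.** A reader might infer that counting from the trauma distorts the treatment contrast. It does not in expectation, because the added interval is fixed before randomisation. The cost is noise and a number that does not match the endpoint. The size of the noise depends on the assumed SDs. The larger increases need an in-hospital SD of 2 to 3 h, and the lognormal of step 2 implies only about 6.5%.

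**The shift is modest.** With 175 patients per arm, the 0.44 h shift has a standard error of about 0.35 h (z about 1.2), and the 0.10 h shift has z about 0.3. Neither would normally produce a significant result alone. The documents give no early mortality rate to support the large contrast. If treatment lowers early death, the shift runs against it. A spurious benefit requires treatment to raise early death, and mortality is compared separately. All of this stands and limits the weight of the point.

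**Patients without a procedure.** They lack a time because of how the endpoint is defined, not because of the t test, and a competing-risks analysis alone does not settle how to count them. This also stands, and the fix has to address it.

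**Conclusion.** The conflict of origin is certain on the text: admission in the objectives, trauma in the analysis, nothing in the outcome list. Any later analysis plan must depart from one of the two. The effect is a mismatched estimate and added variance, about 6.5% to 25% under the assumed SDs.

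The method is poorly matched to the endpoint. The article fixes a test for complete durations, gives no rule for death before control, and yet recognises early death as a source of bias for its primary outcome. Whether this would distort the result depends on an unstated rule and on unequal early mortality: about 0.4 h at an assumed extreme contrast, about 0.1 h at a mild one, nil at equal hazards.

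The documents do not support a claim that the trial's main conclusion is at risk. This is one of eleven listed secondary outcomes, and it drives neither the sample size nor the primary analysis. The point should be corrected before unblinding.

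**What to change.** 1. State one time origin in Objectives {7}, Outcomes {12} and Secondary outcome analysis: admission, as the objectives already have it, or randomisation.
2. Replace the t test by a time-to-control analysis in all randomised patients, with death before control as a competing event: cumulative incidence by arm and Gray's test. A rank test with a pre-stated worst rank for death before control is an acceptable alternative.
3. State how patients who have no surgical or radiological procedure are counted. The current definition gives them no event, and without a rule they would simply appear as never controlled.

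The cost is wording only. Haemorrhage control is already assessed hourly to 6 h and again at 12 and 24 h (Participant timeline {13}). The planned Kaplan-Meier comparison of mortality implies that times of death are recorded, although the article does not say so directly.

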##### Calculation of the cost of each of the strategies

An average cost of care will be calculated for each group. Micro-costing and gross-costing methods will be used to reconstitute the cost of the hospital stay. Thus, data on the consumption of care will be collected prospectively throughout the entire length of the stay in intensive care (the number and nature of blood products and drug treatments used, additional examinations performed, and the length of stay in each care unit). In this way, we can calculate an average cost of the resuscitation stay in each group. The cost of the overall stay will be reconstituted using the modified GHM method, and it will be based on hospital cost accounting data (calculated within the framework of the ENC: national scale of costs).

Comparison of the cost of the two strategies: The difference in costs between the groups will be tested by a Student’s test or by a non-parametric test (Mann-Whitney tests) in case of non-Gaussian distribution. The choice of the test will be made with regard to the distribution of costs in each group (Shapiro-Wilk test, on raw data or, if necessary, on transformed data). If the distribution of costs is not Gaussian, the construction of the confidence interval of the average cost will be based on the non-parametric bootstrap method.

Deterministic and probabilistic sensitivity analyses will be performed to test the robustness of our estimates. Multivariate analyses will also be implemented to take into account censoring (death and follow-up time) in our cost analyses.

Mortalities at 24 h and 28 days will be compared between the two groups using the Kaplan-Meier model. Length of stay will be compared with a Student’s *t* test (if the application conditions are not met, we will use a non-parametric test).

The GOSE at 28 days will be compared with a Student’s *t* test (if the application conditions are not met, we will use a non-parametric test). The locations of the patient’s hospitalization at 28 days will be compared between the two groups using the chi^2^ test (when the application conditions of the chi^2^ test are not met, Fisher’s test will be used).

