#### Sample size {14}

Total blood consumption was estimated in the control group based on 1-year consumption in Grenoble University Hospital and Annecy General Hospital; we found that patients with our eligibility criteria received 12 units on average of RBC, FFP, and platelets. We consider a reduction of 3 units as clinically significant since 3 units represent 1 L of blood products. Thus, a 25% decrease in transfused blood products in the first 24 h is expected (from an average of 12 transfused units in the control group to 9 transfused units in the experimental group). The study needs to include 162 patients per group to demonstrate this 25% reduction with 80% power and α-risk of 0.05, bilateral test (nQuery, Sample Size and Power Calculation, “Statsols”, Statistical Solutions Ltd., Cork, Ireland, blood product units transfused do not follow a normal distribution). To compensate for the estimated lost-to-follow-up, the trial plans to include 350 patients.

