### Statistical methods

#### Statistical methods for primary and secondary outcomes {20a}

The risk of alpha error corresponds to a usual threshold: 5%. All our tests will be bilateral. The initial characteristics of the patients will be represented in a comparative table according to the two treatment groups. Quantitative and qualitative variables will be presented with the usual parameters, mean, and standard deviation as well as numbers and percentages.

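### The fallback test for costs, and the treatment of death as censoring, do not address the mean cost difference that the economic analysis is meant to estimate

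*Protocol article*

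**What the plan says.** The section on calculating the cost of each strategy computes a mean cost for each group. The difference between groups is tested by Student's test "or by a non-parametric test (Mann-Whitney tests) in case of non-Gaussian distribution". The choice depends on a Shapiro-Wilk test of each group's costs, raw or, if needed, transformed. Where costs are not Gaussian, a non-parametric bootstrap gives the confidence interval for the average cost. Deterministic and probabilistic sensitivity analyses follow, with multivariate analyses intended "to take into account censoring (death and follow-up time) in our cost analyses".

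Outcomes {12} defines the economic outcome as "cost of each strategy at days 8 and 28". The costing section instead collects resource use "throughout the entire length of the stay in intensive care" and rebuilds the cost of the overall stay from hospital accounts, without restating days 8 and 28. Objectives {7} names cost-effectiveness as a secondary objective. On testing in general, section {20a} says "All our tests will be bilateral", at the 5% level.

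**The concern.** A budget holder needs the arithmetic mean cost, because the mean times the number of patients is the bill. The plan recognises this by calculating averages. Mann-Whitney asks a different question: whether a randomly chosen PCC patient tends to cost more or less than a randomly chosen control patient. With skewed costs the two answers can differ. The report could then show a mean difference beside a p value that does not test it, and no interval for the difference to settle the matter.

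Death raises a separate problem. Censoring means that later costs exist but were not seen. After death there are none, so the cost to day 28 is fully known. A method that censors at death estimates what patients would have cost had they survived. In severe haemorrhage, with early deaths, that can hide a real difference if mortality differs between arms.

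Finally, the horizon and the objective are not described consistently across the three sections.

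**Working it through.** **Inputs.** The article gives no cost mean, cost SD or economic sample size. Its one design calculation, "The study needs to include 162 patients per group to demonstrate this 25% reduction with 80% power and α-risk of 0.05, bilateral test", concerns transfused units and states no SD; nothing here depends on it. The planned total of 350 gives 350 / 2 = 175 per arm. All cost distributions and mortality rates below are assumptions.

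**1. Which branch applies.** With log-normal costs and 175 per arm, Shapiro-Wilk rejected normality of raw costs in 82% of simulated samples at log-SD 0.2, 99% at 0.3 and 100% from 0.4 upward. Mild skew is enough to reach Mann-Whitney.

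**2. What that branch tests.** For log-normal costs with mean m and log-SD s, the log-scale mean is μ = ln m − s²/2, and

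P(PCC cheaper) = Φ[(μ_control − μ_PCC) / √(s_control² + s_PCC²)].

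Take means of 30 (control) and 33 (PCC), with log-SDs 0.7 and 1.1:
- μ_control = 3.401 − 0.245 = 3.156
- μ_PCC = 3.497 − 0.605 = 2.892
- P(PCC cheaper) = Φ(0.265 / 1.304) = 0.580

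PCC is dearer by 3 on average, yet Mann-Whitney leans towards PCC being cheaper. A t test on logged costs compares 3.156 with 2.892, that is, geometric means of 23.5 and 18.0, and leans the same way. The option to transform does not remove the problem.

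**3. How often it matters at trial size** (3,000 runs per row, 175 per arm):

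| Means, control / PCC | Log-SD, control / PCC | P(PCC cheaper) | Mann-Whitney significant for PCC cheaper | Same, and PCC sample mean higher |
|---|---|---|---|---|
| 30 / 30 | 0.7 / 1.0 | 0.583 | 77% | 27% |
| 30 / 33 | 0.7 / 1.1 | 0.580 | 74% | 49% |
| 30 / 33 | 0.7 / 0.8 | 0.492 | 0.9% | 0.1% |
| 30 / 33 | 0.7 / 0.7 | 0.462 | 0.1% | 0% |

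**4. A gentler change of shape.** Suppose control costs have mean 30,000 and log-SD 1, PCC adds 1,500 to every patient, and the excess above the 75th percentile falls by 25%.
- μ = ln 30,000 − 0.5 = 9.809
- 75th percentile = exp(9.809 + 0.6745) = 35,719
- Mean excess above it = 30,000 × Φ(1 − 0.6745) − 35,719 × 0.25 = 9,898
- Change in mean = 1,500 − 0.25 × 9,898 = −975
- Change in median = +1,500, since the median lies below the 75th percentile
- P(PCC cost > control cost) = 0.526, by simulation

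The directions differ, but at 175 per arm the standard error of the mean difference is about 3,800. Mann-Whitney was significant for PCC being dearer in 13% to 15% of runs, and in only about 1.6% was the PCC sample mean lower at the same time.

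**5. Death as censoring.** Assume an initial cost of 10 units plus 1.5 per day in hospital to day 28, gamma lengths of stay (shape 2, scale 9), and deaths at an exponential time with mean 2 days. The censored estimator sums the mean daily cost among patients still alive.

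| Mortality, control / PCC | True mean difference | Difference when death is censored |
|---|---|---|
| 25% / 20% | +1.06 | +0.05 |
| 25% / 15% | +2.05 | +0.03 |

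With equal mortality both columns gave about 0.05, which is simulation noise. The real difference is erased, not reversed.

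**The case against.** The strongest reply is that the mean is not replaced. Average costs are reported in either branch, the non-Gaussian branch gives them a bootstrap interval, and sensitivity analyses are added. Only the p value answers another question. A reader might infer that the economic result will reverse the mean cost difference. The documents do not support that: frequent contradiction needs clearly unequal spread or shape, and there are no cost data to suggest it. This part of the reply stands, but it does not make Mann-Whitney a test of mean cost or supply an interval for the difference.

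The use of transformed data might avoid Mann-Whitney. It might, but the resulting t test would still not concern arithmetic means.

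Death is named as censoring only for the additional multivariate analyses, and no model is given. That is correct. The main comparison is not described as censoring at death, and the bias shown above assumes one simple estimator. The classification of death as censoring is nevertheless stated in the text.

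A reader might also infer that no cost-effectiveness analysis is planned. A condensed article cannot establish this: Objectives {7} states that aim, and the full protocol or an economic plan may hold the method. What is visible is a mismatch of labels.

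**Conclusion.** The point holds in limited form. The costing section estimates a mean but, in the branch that skewed raw costs would trigger, tests something else and states no interval for the difference in means. The p value can disagree with the mean difference. At 175 per arm with assumed log-normal costs, this ranged from 0.1% of runs or fewer with similar spread, through about 1.6% with a moderate change of shape, to 49% with log-SDs of 0.7 and 1.1. Which case applies here cannot be known from the documents.

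Listing death as censoring is wrong for costs. Under the assumed model it masks a mortality-driven difference of 1.06 to 2.05 units almost entirely; it does not turn it round, and it is confined to supplementary analyses. The differing horizons, and the gap between a cost-effectiveness objective and a cost-only outcome, are inconsistencies to reconcile. The primary analysis is unaffected.

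**What to change.** - Compare arithmetic mean costs whatever their distribution, using a bootstrap 95% confidence interval and test for the difference in means. Drop the Shapiro-Wilk and Mann-Whitney step for costs.
- Set costs after death to zero, and reserve censoring methods for true loss to follow-up.
- State the comparison at day 8 and day 28, as in Outcomes {12}, and say how the intensive-care and overall-stay costings feed into each.
- Either name the effect measure and how it will be combined with cost, or reword the objective in Objectives {7} as a cost comparison.

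This costs some rewording and a little extra analysis. No new data are needed.
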